**Methods:**

Thirty adult patients with gastrointestinal tumors during or after treatment, relevant CRF (Hornheide questionnaire) and life expectancy > 1 year, are enrolled. Patients are randomized to treatment or sham arm and be informed that they will either feel the stimulation or not. Treatment group will receive left-sided tragus above-threshold stimulation with 25 Hz, 250 µs pulse width, and 28-s/32-s on/off paradigm for 4 h throughout the day for 4 weeks. Sham group will receive no stimulation via a nonfunctional electrode. A daily stimulation protocol with time and average intensity is automatically created by a smartphone app connected to the stimulator via Bluetooth®. Multidimensional Fatigue Inventory-20, Short-Form 36 and Beck Depression Inventory questionnaires will be filled out before and after 4 weeks of stimulation.

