### Aim

It is the aim of the study to investigate whether 4 h of daily taVNS is accepted as a treatment against CRF and whether the symptoms of CRF and QoL can be influenced by taVNS in patients with gastrointestinal tumors and clinically apparent CRF.Primary endpoint: Acceptance of and compliance to taVNS, measured with the mean duration of taVNS per day. taVNS, is considered accepted when at least 80% of patients use the stimulator an average of at least 2 h per day.Secondary endpoint: Effect of taVNS on clinical scores (MFI20, BDI, and SF-36)

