#### Study plan

As explained in the SPIRIT table (Table 1), all patients with gastrointestinal tumors are routinely screened for CRF with the Hornheider’s questionnaire. If CRF is detected (severity grade > 4 and a disability score > 5) and the patient could be eligible to participate (inclusion/exclusion criteria), he/she is informed about the study and receives a study flyer. If the patient wants to participate, he/she gets an appointment at the outpatient clinic of the Neurosurgical Department of the University Medical Center Knappschaftskrankenhaus Bochum.

### Visit 0

At this time, the patient will give his informed consent. Then he/she receives the stimulator and is instructed how to use it. He/she is also asked to install the manufacturer’s app on the smartphone (“tvns patient” on Google Play® and Apple App Store®). The stimulator is paired with the smartphone app, logs the stimulation intensity and duration for each day, and reminds the patient to stimulate. The data of the app can only be read by the patient and will be documented by the physician at the end of the study, together with the patient.

Personal data like age, sex, height, and weight will be recorded. Also, it will be noted whether the patient is still under radio- or chemotherapy. The three questionnaires are filled out, and the patient is discharged. After 1 week, he/she will be called by our study nurse and asked if he/she has any questions or problems with the stimulation. The last visit will be 4 weeks later. The patients are advised to contact the principal investigator whenever a side effects occur.

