### 4-week-stimulation phase

#### Visit 1

After 4 weeks, the patient has a new appointment at the outpatient clinic of the Neurosurgical Department. The questionnaires are filled out, and the stimulation statistics are read from the smartphone app, under the patient’s supervision. The patient’s weight is measured again. If a patient is unable to physically appear to the second visit, he/she will be given a temporary patient’s access to the respective REDCap® eCRF to fill out the missing questionnaires. The stimulator is given back to the hospital.

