### Statistical analysis

For the descriptive analyses of the primary endpoint and all binary secondary endpoints absolute numbers, percentages and 95% confidence interval (CI) using Agresti-Coull method will be calculated. For comparisons between groups, odds ratio and corresponding 95% CI will be calculated. For continuous secondary endpoints mean, standard deviation and the 95% CI for the mean or median and quartiles will be calculated. For comparisons, difference between means and corresponding 95% CI or difference in location parameters using the Hodge-Lehman method and corresponding 95% CI will be determined. Furthermore, for the primary endpoint, we will test the null hypothesis “acceptance rate is higher than 80%” with an exact one-sided binomial test with significance level 5%.

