## Discussion

### Endpoints

The main objective and primary endpoint of the presented feasibility study protocol are to investigate the adherence of patients to daily stimulation of the left ear during daily routine. A positive adherence will be stated if at least 80% of the participants use the stimulation at least 50% of the recommended time (4 h) per day. The second generation of in-ear electrodes for the tVNS-L system provides a fixation ring which is put around the earlobe to provide better stability compared to the NEMOS® system. A recent study with NEMOS® reported a high drop-out rate due to practical reasons [50], and to our knowledge, our study will be the first to systematically investigate adherence to the protocol with the new electrode. Furthermore, it will be the first to evaluate therapy adherence by using the newly developed and published smartphone apps which provide an automatic stimulation diary. Last, patients suffering from fatigue are harder to motivate to participate in studies. It therefore will be of great interest if they will adhere to a daily stimulation protocol of 4 h over a period of 4 weeks.

Our findings will give us the information needed for a future randomized control trial, such as recruitment rates, inclusion/exclusion criteria, adherence to the therapy, and sample size. It will also provide insight on how oncological patients suffering from fatigue can handle a daily stimulation protocol and which questionnaires will be the most sensitive for the investigation of taVNS in a CRF population. To this end, the secondary endpoints are the respective questionnaires for fatigue and QoL.

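### The questionnaire scores are compared between arms with no baseline covariate although each is measured at baseline; with 15 per arm, ANCOVA would give a more precise estimate at almost no cost

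*Protocol article*

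**What the plan says.** The Statistical analysis section of the protocol article sets the between-group comparison for continuous secondary endpoints: "For comparisons, difference between means and corresponding 95% CI or difference in location parameters using the Hodge-Lehman method", with a 95% confidence interval for either. It names no model and no covariate. It also does not say whether the quantity compared is the week-4 score or the change from baseline.

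The Aim section makes MFI20, BDI and SF-36 the secondary endpoint. All three are measured twice. The abstract says: "Multidimensional Fatigue Inventory-20, Short-Form 36 and Beck Depression Inventory questionnaires will be filled out before and after 4 weeks of stimulation". Visit 0 confirms the baseline measurement ("The three questionnaires are filled out, and the patient is discharged"), and Visit 1 the one after 4 weeks ("The questionnaires are filled out, and the stimulation statistics are read from the smartphone app").

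The sample size section gives 15 patients per arm, chosen on feasibility, with no SD or effect size for any questionnaire. The Patients section describes automatic randomisation in REDCap and mentions no stratification by baseline score. Under Endpoints in the Discussion, the findings are to inform a future trial and to show "which questionnaires will be the most sensitive for the investigation of taVNS in a CRF population".

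**The concern.** When an outcome is measured before and after treatment, the baseline value usually explains part of the variation at follow-up. A comparison that omits it as a covariate leaves that variation in the standard error. It also lets any chance difference between the arms at baseline pass into the estimated effect. In a large trial both effects are small, but with 15 per arm they need not be.

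At stake is the quality of the pilot's only evidence on fatigue, depression and quality of life, which the Discussion wants to carry forward into planning a larger trial. The method is a stated choice with a concrete better alternative that uses data already collected.

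**Working it through.** **No figure to reproduce.** The protocol's power and interval-length figures concern the acceptance rate. It gives no SD, power or precision for the questionnaires.

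**Inputs.**
- n = 15 per arm (Justification of sample size), all assumed to have both measurements.
- Outcome SD = 1, equal at baseline and week 4, so results are in SD units (assumption).
- Baseline-to-week-4 correlation r: not in the documents; 0.3, 0.5 and 0.7 assumed.

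**Formulas for the width of the 95% interval for a mean difference.**
- Week-4 scores: 2 × t(28) × √(2/15).
- Change scores: the same × √(2(1 − r)).
- ANCOVA: 2 × t(27) × √[(2/15)(1 − r²)(1 + 1/26)]. The last factor is the small-sample cost of estimating the slope.

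With t(28) = 2.048 and √(2/15) = 0.365, the week-4 width is 2 × 2.048 × 0.365 = 1.496. For ANCOVA at r = 0.5, with t(27) = 2.052, it is 2 × 2.052 × √(0.1333 × 0.75 × 1.0385) = 2 × 2.052 × 0.322 = 1.322.

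| r | Week-4 scores | Change scores | ANCOVA | ANCOVA narrower than week-4 | ANCOVA narrower than change |
|---|---|---|---|---|---|
| 0.3 | 1.496 | 1.770 | 1.457 | 3% | 18% |
| 0.5 | 1.496 | 1.496 | 1.322 | 12% | 12% |
| 0.7 | 1.496 | 1.159 | 1.090 | 27% | 6% |

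By the large-sample variance ratio 1 − r², 15 per arm with ANCOVA is worth 15/(1 − r²) = 16.5, 20.0 and 29.4 per arm analysed on unadjusted week-4 scores.

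**Where the gain stops.** Let k = [t(27)/t(28)]² × (1 + 1/26) be the small-sample penalty. ANCOVA is narrower than the week-4 comparison when r exceeds √(1 − 1/k), about 0.20. It is narrower than the change-score comparison when r is below 2/k − 1, about 0.92.

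**Chance baseline imbalance.** The standard error of the baseline difference is √(2/15) = 0.365 SD. The probability that it exceeds 0.5 SD in either direction is 2 × [1 − Φ(0.5/0.365)] = 17% for each score. An imbalance of 0.5 SD shifts the week-4 difference by 0.5r = 0.15, 0.25 and 0.35 SD for the three correlations. It shifts a change-score difference the opposite way by 0.5(1 − r) = 0.35, 0.25 and 0.15 SD. ANCOVA removes the linear part of this shift.

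These widths are for a difference in means; the Hodges-Lehmann option was not computed.

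**The case against.** The strongest reply is that nothing in the plan is wrong. Under randomisation an unadjusted difference is unbiased on average and its interval is valid. The questionnaires are secondary, no hypothesis test is stated for them, the sample size rests on feasibility, and no stated decision would change if the interval were 1.32 rather than 1.50 SD wide. The article is condensed, and an analysis plan may specify covariates. The gain also depends on an undocumented correlation. Recruiting on fatigue severity may lower that correlation, and at 0.3 the gain over week-4 scores is only 3%.

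Most of this stands, and it limits the severity. It does not remove the point: the article does state a comparison method, and that method has no baseline covariate.

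Four stronger readings might be inferred, and the documents do not support them.
- *The baseline score is ignored altogether.* The text does not settle this. A change-score reading is open, and under it the gain at r = 0.7 is 6%, not 27%.
- *The estimate is biased or its interval invalid.* The shift arises within a given imbalanced sample. It is not a bias over repeated randomisation.
- *The plan cannot compare how sensitive the questionnaires are.* Means, SDs and differences are among the planned summaries for each scale, so standardised differences can be derived from them.
- *The group difference will set the next trial's sample size.* Sample size is listed among what the findings will inform, but that specific input is not named.

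A formal ranking of the three questionnaires by standardised effect would also be unsound. At r = 0.5 each adjusted effect has a standard error of about 0.32 SD. Selection on fatigue severity and on no or stable depression may compress the baseline SDs unequally.

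**Conclusion.** The point holds as a matter of efficiency, not validity. The stated comparison uses no baseline covariate although the baseline scores are available, and it leaves open whether scores or changes are compared. ANCOVA gives a narrower interval under either reading over the whole assumed range of 0.3 to 0.7: by 3% to 27% against week-4 scores, and by 18% down to 6% against change scores. It also protects against a baseline imbalance that, with 15 per arm, exceeds half an SD about one time in six for each score. The sizes rest on the assumed correlation, equal SDs at both visits, a linear relation with a common slope, and complete data. Because these are secondary endpoints of a feasibility pilot, the severity is minor to moderate.

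**What to change.** In the Statistical analysis section, state that for each questionnaire score the group difference at week 4 will be estimated by ANCOVA, with the week-4 score regressed on arm and baseline score, and reported with its 95% interval as the main secondary analysis. Keep the unadjusted mean difference or the Hodges-Lehmann estimate as a sensitivity analysis, and say whether it is applied to week-4 scores or to changes. For the goal of finding the most sensitive questionnaire, standardised differences with their intervals may be reported descriptively, with a note that they do not support a firm ranking.

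The cost is a change of wording and one degree of freedom. No new data, visits or patients are needed.

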## Discussion

### Endpoints

The main objective and primary endpoint of the presented feasibility study protocol are to investigate the adherence of patients to daily stimulation of the left ear during daily routine. A positive adherence will be stated if at least 80% of the participants use the stimulation at least 50% of the recommended time (4 h) per day. The second generation of in-ear electrodes for the tVNS-L system provides a fixation ring which is put around the earlobe to provide better stability compared to the NEMOS® system. A recent study with NEMOS® reported a high drop-out rate due to practical reasons [50], and to our knowledge, our study will be the first to systematically investigate adherence to the protocol with the new electrode. Furthermore, it will be the first to evaluate therapy adherence by using the newly developed and published smartphone apps which provide an automatic stimulation diary. Last, patients suffering from fatigue are harder to motivate to participate in studies. It therefore will be of great interest if they will adhere to a daily stimulation protocol of 4 h over a period of 4 weeks.

Our findings will give us the information needed for a future randomized control trial, such as recruitment rates, inclusion/exclusion criteria, adherence to the therapy, and sample size. It will also provide insight on how oncological patients suffering from fatigue can handle a daily stimulation protocol and which questionnaires will be the most sensitive for the investigation of taVNS in a CRF population. To this end, the secondary endpoints are the respective questionnaires for fatigue and QoL.

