### Objectives

Based on the abovementioned observations that CRF might be caused by inflammatory processes which may be modulated by taVNS, it is the aim of this feasibility study to investigate whether daily taVNS is accepted by the patients as a treatment against CRF during this 4-week trial. Additionally, we will evaluate whether CRF can be influenced by left-sided taVNS. Established and sensitive questionnaires for depression, fatigue, und QoL will be used: Short-Form 36 (SF-36), Beck Depression Inventory (BDI), and Multidimensional Fatigue Inventory (MFI20). We chose this combination of questionnaires with respect to both the sensitivity for changes during taVNS and to the length and number of questions.

The SF36 questionnaire is established in many diseases. It is commonly applied in patients with fatigue [28, 29], autoimmune diseases [30, 31], Parkinson’s [32], and cancer [33–36]. It comprises 36 questions focusing on general aspects of QoL and will be applied to investigate the general wellbeing of our patients before and after taVNS. BDI examines the existence of depression and has already proven to respond to iVNS in epilepsy patients [37], to cervical noninvasive VNS in migraine patients [38], and to taVNS in patients with depression [39]. MFI20 is an established questionnaire in the assessment of cancer-related fatigue [40, 41]. Additionally, baseline values for a general population [42] and minimal clinically important differences are available [43, 44].

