### Justification of sample size

Acceptance and compliance are considered successful when at least 80% of patients fulfills the acceptance criteria as defined in the primary endpoint. A total of 30 patients will be recruited, 15 in each of the two groups “sham” and “stimulation.” The sample size of 15 subjects per group was based on feasibility, as taVNS against cancer-related fatigue has not been investigated before. It is also based on studies investigating non-invasive VNS against sleep deprivation [45], lupus [46], and Sjoegren syndrome [47]. The choosen sample size adheres to the recommendations of sample sizes in feasibility studies [48, 49]. We will probably see a power of approximately 80% to detect if less than 50% of the patients fulfills the acceptance criteria with an exact one-sided binomial test at significance level 5%. Furthermore, with this sample size, the expected length of the 95% confidence interval for the adherence rate within one group lies between 0.38 and 0.44 and between 0.28 and 0.33 for the pooled rate. The expected length was calculated using the Agresti-Coull method and assuming a true rate between 50 and 80%.

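### The study is meant to give insight into which questionnaire is most sensitive to taVNS, but the planned contrasts are in each questionnaire's own points and cannot be compared as reported

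*Protocol article*

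**What the plan says.** The Endpoints part of the Discussion lists what the pilot should deliver for a later randomised trial. One item begins "It will also provide insight on how oncological patients suffering from fatigue can handle a daily stimulation protocol" and goes on to "which questionnaires will be the most sensitive for the investigation of taVNS in a CRF population". The next sentence gives this as the purpose of having the fatigue and quality-of-life questionnaires as secondary endpoints. The Aim section names three instruments: MFI20, BDI and SF-36.

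The Statistical analysis section describes each arm as follows: "For continuous secondary endpoints mean, standard deviation and the 95% CI for the mean or median and quartiles will be calculated". Between arms it plans "difference between means and corresponding 95% CI or difference in location parameters using the Hodge-Lehman method and corresponding 95% CI". It names no standardised effect, no adjustment for the Visit 0 score and no comparison between instruments. The Objectives section says, for MFI20 only, that "minimal clinically important differences are available", and the analysis section does not use them.

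On size: "A total of 30 patients will be recruited, 15 in each of the two groups". The Justification of sample size bases this on feasibility. Its power and confidence-interval figures concern acceptance of the stimulation, not the questionnaires.

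**The concern.** Sensitivity to treatment is a matter of signal relative to noise, so comparing instruments needs a common scale. A difference of, say, 4 points on MFI20 and 4 points on BDI (illustrative values) does not show which instrument responds more. The analysis section also allows a mean difference or a location shift without saying that the same choice applies to every questionnaire, so the contrasts could differ in kind as well as in units. A quality-of-life scale and symptom scales may also run in opposite directions.

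At stake is the choice of endpoint for the next trial. If it draws on this pilot, it should rest on a measure that addresses the question and comes with a statement of its uncertainty.

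**Working it through.** **Is there a figure to reproduce?** No. The article gives no effect size, SD or precision for any questionnaire. The calculations below show what a common-scale analysis could deliver at the planned size.

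**Inputs.** From the article: n = 15 per arm, three instruments, scores at Visit 0 and Visit 1 (4 weeks). Assumed, because the article gives none: true standardised effects, the correlation r between the estimated effects on two instruments, and the correlation c between baseline and 4-week score.

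**1. Precision for one instrument, unadjusted.**
SE(d) ≈ √(2/n) = √(2/15) = 0.365, so the 95% half-width is 1.96 × 0.365 = 0.716 SD. With the extra term d²/(4n), an observed d of 0.5 has SE 0.371 and a 95% CI of −0.23 to 1.23.

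**2. Gain from baseline adjustment.**
The SE shrinks by about √(1 − c²).
- c = 0.5: 0.716 × 0.866 = 0.62 SD
- c = 0.7: 0.716 × 0.714 = 0.51 SD

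**3. Precision for the difference between two instruments, unadjusted.**
SE = 0.365 × √(2(1 − r)).
- r = 0.5: half-width 0.716 SD
- r = 0.6: half-width 0.640 SD
- r = 0.7: half-width 0.554 SD

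A simulation that also estimates the SDs gives slightly wider values for a first instrument with a true effect of 0.5 and a second with 0.3: 0.76 at r = 0.5 and 0.59 at r = 0.7.

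**4. How often the truly best instrument has the largest estimate** (40,000 simulated trials, unadjusted, 15 per arm; chance is 33%).

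| Assumed true effects | r = 0.3 | r = 0.5 | r = 0.7 |
|---|---|---|---|
| 0.5 / 0.4 / 0.3 | 47% | 50% | 54% |
| 0.5 / 0.3 / 0.3 | 53% | 56% | 62% |
| 0.8 / 0.5 / 0.2 | 71% | 76% | 83% |

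The result depends heavily on the assumed pattern, so no single row should be quoted as the performance of this trial.

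**5. What the planned output allows.** On the mean-based route, the difference divided by the pooled SD gives d. On the median route, quartiles and a Hodges-Lehmann shift do not readily give d. On neither route do the summaries contain the within-patient correlation between instruments. The term r in step 3 is therefore missing, and an interval for the difference between two instruments needs patient-level data.

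**The case against.** Four counter-arguments have weight.

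*The mean-based output is enough.* With means, SDs and a CI for the difference, a scale-free effect follows by simple division, and for the same patients it orders the instruments. This stands. A reader might infer that the planned results can never be compared; that is too strong. The gap is in the contrasts as reported, in the median route, and in the uncertainty of the comparison.

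*No ranking is promised.* A reader might infer that the trial undertakes to show which questionnaire is best. The text offers insight, within a feasibility study, in a Discussion paragraph. The Aim section does not list questionnaire sensitivity as an endpoint. This also stands. But the same paragraph gives this insight as the purpose of the secondary endpoints, so an analysis that addresses it is a fair request.

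*Fifteen per arm is not a defect.* The size is justified by feasibility and no power is claimed for the questionnaires. Wide intervals contradict nothing in the article; they only bear on how the comparison is described.

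*The detail may sit in a document not shown.* A full protocol or analysis plan may define a standardised effect. The point therefore rests on the measures the article does name for continuous secondary endpoints and on how poorly they suit the purpose it states. It does not rest on missing detail.

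One further temptation is a rule that no questionnaire may be called most sensitive unless its pairwise interval excludes zero. For a true gap of 0.2 SD and r of 0.5 to 0.7, that would be met in only about 8 to 11% of trials per pair. It is a poor rule for an exploratory comparison and is not recommended.

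**Conclusion.** The point holds as a mismatch between a stated aim and the named analysis. The Discussion looks to the secondary endpoints for insight into questionnaire sensitivity, while the analysis section fixes only raw-scale contrasts with no baseline adjustment named.

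Even on a common scale the comparison would be imprecise. The unadjusted half-width is about 0.72 SD per instrument, or about 0.5 to 0.6 SD with baseline adjustment if c is 0.5 to 0.7. For the difference between two instruments it is about 0.55 to 0.72 SD, unadjusted, if r is 0.5 to 0.7. These correlations are assumptions; the 0.72 follows from 15 per arm alone.

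Severity is minor. The acceptance endpoint, its test and the conduct of the trial are untouched.

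**What to change.** In Statistical analysis:
- Use the same estimator for every questionnaire: the between-arm difference at 4 weeks adjusted for the Visit 0 score.
- Score each instrument so that a positive value means improvement.
- Report the result in raw points and as a standardised effect, each with a 95% CI.
- Name the standardising SD in advance. Pooled baseline SD is not an automatic choice: patients are selected on fatigue severity and on no or stable depression, which may narrow the baseline spread differently across instruments.
- Optionally, add patient-level bootstrap intervals for the differences between instruments' standardised effects.

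In Discussion, Endpoints: say that the comparison of questionnaires is exploratory, and give the expected precision at 15 per arm.

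The cost is a few lines of analysis on data already collected at Visits 0 and 1, with no extra patients or assessments, and a more modest sentence in the Discussion.
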